| Statistical analysis | 
Statistical data analysis is performed using IBM SPSS software, version 26.0 (IBM Corporation, Armonk, NY, USA) and Tobii Pro Lab Analyser (Tobii, Danderyd, Sweden). The statistical significance level is defined by a p-value of <0.05. An attempt is made to avoid missing data by inspecting the questionnaires after completion and, in case of unanswered items, asking the study participants to complete them. The number of missing data is noted; due to the less sensitive topic of the study, it is assumed that missing variable values can be assigned to "missing completely at random" or "missing at random". An intention-to-treat analysis is performed for all cases analysed in their originally assigned group.
 
Descriptive statistics are used for demographic data and primary and secondary outcomes. Counted and nominal scaled data (gender, fall rate, recruitment, retention and adherence rate, number of missing data if applicable, number of adverse events) are reported as whole numbers or percentages. Ordinal scaled variables (MMSE, UPDRS, H & Y, FGA, BBS, PDQ-39, FOGQ, FES-I, BDI-II) are expressed as median (minimum, maximum or interquartile range) and metric variables (TUG, TUGman, FSST, 10MWT, eye movements: Saccade velocity, amplitude, latency, fixation duration) by mean (95% confidence interval, CI or standard deviation, SD). The data is also presented graphically (e.g. by bar charts, box plot or line graphs).
 
The eligibility rate (%) is the percentage of patients suitable for the study after applying the inclusion and exclusion criteria from the Parkinson's patients treated at the Reha Zentrum Münster
 |

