|  | 
during the study period.
 
The recruitment rate (%) is determined as follows:
 <math>(N_{\text{Consent}}/N_{\text{Suitable}})*100</math>; where <math>N_{\text{Consent}}</math> is the number of participants who signed the informed consent form; <math>N_{\text{Suitable}}</math> is the number of patients suitable for the study based on the inclusion and exclusion criteria.
 
The retention rate (%) is calculated as follows:
 <math>(N_{\text{Completed}}/N_{\text{Total}})*100</math>; where <math>N_{\text{Completed}}</math> is the number of participants who completed the study; <math>N_{\text{Total}}</math> is the total number of participants in the study.
 
The adherence rate (%) is determined as follows: (Actual number of exercise sessions/planned number of training sessions)*100 (Osterberg & Blaschke, 2005).
 
Eligibility, recruitment, retention and adherence rates are calculated using the Wilson 'score' method propagated by Newcombe, together with its 95% CI (Newcombe, 1998) In the case of a proportion close to 0 or 1, a Poisson approximation according to Brown is used. (Brown, Cai, & DasGupta, 2001)..
 
A test for statistically significant differences between groups at baseline is performed: for nominal data (eligibility, recruitment, retention, adherence rates, gender) the Fisher's Exact Test is used, for ordinal data (age, H & Y, UPDRS, FGA, MMST, BBS, PDQ-39, FOGQ, FES-I, BDI-II) the Mann Whitney-U test and for metric data (TUG, TUGman, FSST, 10MWT, eye movements: Saccade velocity, amplitude, latency, fixation duration) the T-test for independent samples. Preliminary inferential statistical analysis to detect trends in intervention effectiveness and as a basis for sample size calculation for a randomised controlled trial with sufficient power of at least 80% (using mean (SD) differences between groups) will be performed. For inferential statistics, metric data are first tested for normal distribution and significant data outliers using the Shapiro-Wilk test, Q-Q plots and histograms. Non-normally distributed data are transformed using suitable transformation (e.g. ln, square root), checked
 |

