## **4 Methods**

### **4.1 Study participants**

#### **4.1.1 Participant recruitment and study inclusion**

All persons with Idiopathic Parkinson's Syndrome treated at the Reha Zentrum Münster during the recruitment period will be reviewed by the medical staff with regard to their suitability for study participation. All persons with idiopathic Parkinson's syndrome who meet the inclusion criteria of this study and do not fulfil any of the exclusion criteria will be informed about the study orally and in writing by the respective investigator. After determining a basic suitability (inclusion criteria) and the patient's consent, i.e. his/her interest in participating in the study, a screening is carried out. Using predefined cut-off scores of the Mini-Mental-Status-Test (MMST) (Folstein et al., 1975)  $\geq 24/30$  points, moderate to severe cognitive impairment is excluded. In the case of the absence of these exclusion criteria, study inclusion will be as described below.

After an appropriate reflection period, opportunity for questions and the patient's consent to participate, the information letter and patient consent form is then dated and signed by both the patient and the doctor. The investigator records the participation on a special patient identification list. This list is used to identify the patient at a later date and contains the patient's identification number (ID), full name, date of birth and date of inclusion in the clinical trial. The patient identification list remains at the trial site after completion of the trial. The ID will be entered with the date of inclusion in the randomisation list as described and prepared by an independent researcher.

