## 5.6 Data analysis

### 5.6.1 Statistical data analysis

Statistical data analysis is performed using IBM SPSS software, version 26.0 (IBM Corporation, Armonk, NY, USA) and Tobii Pro Lab Analyser (Tobii, Danderyd, Sweden). The statistical significance level is defined by a p-value of  $<0.05$ . An attempt is made to avoid missing data by inspecting the questionnaires after completion and, in case of unanswered items, asking the study participants to complete them. The number of missing data is noted; due to the less sensitive topic of the study, it is assumed that missing variable values can be assigned to "missing completely at random" or "missing at random". An intention-to-treat analysis is performed for all cases analysed in their originally assigned group.

Descriptive statistics are used for demographic data and primary and secondary outcomes. Counted and nominal scaled data (gender, fall rate, recruitment, retention and adherence rate, number of missing data if applicable, number of adverse events) are reported as whole numbers or percentages. Ordinal scaled variables (MMSE, UPDRS, H & Y, FGA, BBS, PDQ-39, FOGQ, FES-I, BDI-II) are expressed as median (minimum, maximum or interquartile range) and metric variables (TUG, TUGman, FSST, 10MWT, eye movements: Saccade velocity, amplitude, latency, fixation duration) by mean (95% confidence interval, CI or standard deviation, SD). The data is also presented graphically (e.g. by bar charts, box plot or line graphs).

The eligibility rate (%) is the percentage of patients suitable for the study after applying the inclusion and exclusion criteria from the Parkinson's patients treated at the Reha Zentrum Münster during the study period.

The recruitment rate (%) is determined as follows:  $(N_{\text{Consent}}/N_{\text{eligible}}) \times 100$ ; where  $N_{\text{Consent}}$  is the number of participants who signed the informed consent form;  $N_{\text{eligible}}$  is the number of patients eligible for the study based on the inclusion and exclusion criteria.

The retention rate (%) is calculated as follows:  $(N_{\text{completed}}/N_{\text{Total}}) \times 100$ ; where  $N_{\text{completed}}$  is the number of participants who completed the study;  $N_{\text{Total}}$  is the total number of participants in the study.

Adherence rate (%) is determined as follows: (Actual number of exercise sessions/planned number of training sessions)\*100 (Osterberg & Blaschke, 2005).

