Eligibility, recruitment and adherence rates are calculated using the Wilson 'score' method propagated by Newcombe together with its 95% CI (Newcombe, 1998). In the case of a proportion close to 0 or 1, a Poisson approximation according to Brown is used. (Brown, Cai, & DasGupta, 2001)..

A test for statistically significant differences between the groups at baseline: for nominal data the Fisher's Exact Test is used, for ordinal data the Mann Whitney-U test and for metric data the T-test for independent samples. A preliminary inferential statistical analysis to detect trends in the effectiveness of the intervention and as a basis for sample size calculation for a randomised controlled trial with sufficient power of at least 80% (based on mean differences (SD) between groups) will be performed. For inferential statistics, metric data are first tested for normal distribution and significant data outliers using the Shapiro-Wilk test, Q-Q plots and histograms. Non-normally distributed data are transformed using suitable transformation (e.g. ln, square root), checked again and analysed non-parametrically if normal distribution is missing.

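### The synopsis puts four feasibility rates into a between-group Fisher test at baseline: two are fixed before randomisation, two arise after it, and adherence is defined only in sessions

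*Protocol*

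**What the plan says.** The Study synopsis (Statistical analysis) introduces the rule with "A test for statistically significant differences between groups at baseline is performed" and continues: "for nominal data (eligibility, recruitment, retention, adherence rates, gender) the Fisher's Exact Test is used". Section 5.6.1 repeats the rule without naming variables: "A test for statistically significant differences between the groups at baseline: for nominal data the Fisher's Exact Test is used".

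The rates are defined in the same places:

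- **Eligibility:** "The eligibility rate (%) is the percentage of patients suitable for the study after applying the inclusion and exclusion criteria", taken from the Parkinson's patients treated at the centre.
- **Recruitment:** consenting patients over a denominator that "is the number of patients suitable for the study based on the inclusion and exclusion criteria".
- **Retention:** the numerator "is the number of participants who completed the study"; the denominator is all participants.
- **Adherence:** "Actual number of exercise sessions/planned number of training sessions)\*100".

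Section 4.1.1 places randomisation after consent: "The ID will be entered with the date of inclusion in the randomisation list". Table 2 assigns adherence to the intervention period and retention to the post-intervention and follow-up time points. Both the synopsis and 5.6.1 specify a Wilson interval for the adherence rate.

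**The concern.** A baseline comparison between arms needs variables that have a value for each randomised person at the moment of allocation. Four of the five listed do not meet that condition. For two of them the patients who make the rate informative, those who are ineligible or decline, never have an arm. The other two do not exist until treatment has begun.

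Adherence raises a second question. Fisher's test and the Wilson interval both need counts, and the only counts that the definition supplies are sessions. Sessions from one person tend to be attended or missed together, so pooling them overstates the information.

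Feasibility is the second study objective (section 2.3), and section 4.4.14.1 sets targets of 80% for retention and 75% for adherence. Whether gaze training lowers attendance is something this pilot can inform. A pooled test could present a chance difference as a real one, and a pooled interval could appear to settle the 75% target when the data do not.

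**Working it through.** **Inputs from the protocol.** 17 participants per arm, 34 in total (4.1.2.3); 16 planned sessions each (4.2.1); significance level 0.05 (5.6.1), taken as two-sided because sidedness is not stated; adherence target 75% (4.4.14.1). The within-person correlation (ICC) of attendance is not given and is an assumption, shown over a range.

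**The plan's own figure.** 30/(1 − 10/100) = 33.3, rounded up to 34. This reproduces and is not in dispute.

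**Eligibility and recruitment.** Everyone randomised has been judged eligible and has consented. By arm the table is therefore 17 of 17 against 17 of 17, and Fisher's test gives p = 1 whatever the trial's recruitment was like.

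**Retention and adherence.** By the protocol's definitions and Table 2, neither has a value at baseline.

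**Adherence by pooled sessions.** Sessions per arm: 17 × 16 = 272; in total 34 × 16 = 544. The design effect is DE = 1 + (16 − 1) × ICC, the effective number of sessions per arm is 272/DE, and the approximate type I error of a nominal 5% test is 2 × (1 − Φ(1.96/√DE)). The last column but one is a simulation of beta-binomial attendance with no arm difference, mean attendance 75%, 17 per arm and 3,000 runs per setting, testing pooled sessions by Fisher. The last column applies Mann-Whitney to sessions per participant in the same simulated data.

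| Assumed ICC | DE | Effective sessions per arm | Type I error, formula | Type I error, pooled Fisher (simulated) | Type I error, Mann-Whitney per participant (simulated) |
|---|---|---|---|---|---|
| 0 | 1 | 272 | 5% | 4% | 5% |
| 0.1 | 2.5 | 109 | 22% | 20% | 5% |
| 0.3 | 5.5 | 49 | 40% | 40% | 5% |
| 0.5 | 8.5 | 32 | 50% | 49% | 5% |

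Results were similar with 15 per arm and with 85% attendance.

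**The Wilson interval for overall adherence.** At an observed 75%, 544 sessions treated as independent give 71.2% to 78.5%. Putting the effective number 544/DE into the same formula gives 68.8% to 80.3% at ICC 0.1 (544/2.5 = 217.6) and 65.6% to 82.5% at ICC 0.3 (544/5.5 = 98.9). With 34 as the denominator, the limiting case in which each person attends all sessions or none, it is 58.4% to 86.5%. The proper interval lies between the first and the last, depending on the correlation.

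**The case against.** The strongest reply is that no sentence names the unit for Fisher's test on adherence. The synopsis classes the rate as nominal, which would also fit a yes/no variable per participant, and section 4.4.14.1(c) offers a threshold (75%, three of four sessions a week). On that reading there is no inflation: Fisher on attendance of at least 12 of 16 sessions rejected about 2% of the time in the simulation at 75% attendance. This stands. A reader might infer that the protocol prescribes a session-level test; it does not say so. But no per-participant adherence rate is defined, the definition given counts sessions, and the error about the time point remains on either reading.

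A reader might also infer that none of the four rates can be tested. That goes too far for retention: its unit is the patient, and Fisher's test by arm is valid once it is no longer called a baseline comparison. For eligibility and recruitment the test is empty rather than misleading.

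It is tempting to add that the many other baseline p-values will probably yield a false imbalance. The documents do not support a figure for this. Multiplying up the error rates would need independent tests, while the protocol itself cites correlations of −0.78 between BBS and TUG (4.4.6.2) and −0.72 between TUGman and BBS (4.4.5.2). Nothing in 5.6.1 makes an analysis depend on those p-values. Testing baseline differences is a matter of preference here, not part of the error.

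The wrong list appears only in the synopsis; 5.6.1 names no variables and so neither repeats nor corrects it. Nor is this a detail left to a later analysis plan, because the synopsis already fixes the variables, the test and the time point.

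**Conclusion.** The rule in the synopsis is wrong as written for four of its five nominal variables. This follows from the protocol's own definitions and needs no assumption. The adherence part is conditional: if sessions are pooled, which the only stated definition leads to, the type I error of a nominal 5% comparison is about 20–22% at a correlation of 0.1 and about 40% at 0.3, and the interval for overall adherence is too narrow. Those sizes rest on an assumed correlation.

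The consequence is confined to feasibility reporting. The adherence and retention targets are single overall thresholds, no stated criterion uses a between-arm p-value for them, and the analysis of the Functional Gait Assessment is untouched. The change is still worth making, because feasibility is one of the four study objectives.

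**What to change.** 1. In the synopsis, remove eligibility, recruitment, retention and adherence from the baseline test, and align the text with 5.6.1.
2. Report eligibility and recruitment once, for the whole sample, each with a Wilson 95% interval.
3. Compare retention by arm as an outcome, by Fisher's exact test or a risk difference with 95% CI.
4. Define adherence per participant as the percentage of the 16 sessions performed. Compare arms by Mann-Whitney with a Hodges-Lehmann 95% CI, and base the interval for overall adherence on the participants' values, not on the session count.

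Presenting baseline data without p-values is optional. The changes are to wording only and need no new data. The price is a wider interval for adherence, which may leave the 75% target less clearly met or missed.

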|                  | 
again and analysed non-parametrically if normal distribution is missing.
 
Differences between the two groups and test times are calculated for ordinal data as follows: New variables are generated from the difference between the post-intervention and baseline data. The difference between group 1 and 2 is determined using the Mann Whitney-U test. For the ordinal variables FES-I and FOGQ, which are also collected at the follow-up call, a Kruskal Wallis test is performed across all groups and test time points. Changes in fall rate (nominal) between baseline, post-intervention and follow-up will be calculated using Chi-Square test. Metric data will be tested for homogeneity of variance (Levene test) as the basic assumption of a 2 x 2 ANOVA, with "time (baseline, post-intervention)" as the within-factor and "group (1, 2)" as the between-factor. If there is no homogeneity of variance, an alternative F-statistic (e.g. according to Welch or Brown-Forsythe) is used. If the basic assumption of sphericity is not fulfilled, corrected values are used, e.g. according to Greenhouse-Geisser or Huynh-Feldt. To calculate the differences between the groups and measurement times, a 2 x 2 ANOVA (analysis of variance) is performed, followed by pairwise comparisons (Bonferroni correction for all comparisons) between the groups at measurement times 1 and 2 if statistical significance is present. In the case of failure of the adaptive measures, non-parametric tests are used as described for ordinal scaled data. Effect size is reported using partial Eta squared and standardised effect size.
 |

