Differences between the two groups and test times are calculated for ordinal data as follows: New variables are generated from the difference between the post-intervention and baseline data. The difference between group 1 and 2 is determined using the Mann Whitney-U test. For the ordinal variables FES-I and FOGQ, which are also collected at the follow-up call, a Kruskal Wallis test is performed across all groups and test time points. Changes in fall rate (nominal) between baseline, post-intervention and follow-up will be calculated using Chi-Square test. Metric data will be tested for homogeneity of variance (Levene test) as the basic assumption of a 2 x 2 ANOVA, with "time (baseline, post-intervention)" as the within-factor and "group (1, 2)" as the between-factor. If there is no homogeneity of variance, an alternative F-statistic (e.g. according to Welch or Brown-Forsythe) is used. If the basic assumption of sphericity is not met, corrected values are used, e.g. according to Greenhouse-Geisser or Huynh-Feldt. To calculate the differences between the groups and measurement times, a 2 x 2 ANOVA (analysis of variance) is performed, followed by pairwise comparisons (Bonferroni correction for all comparisons) between the groups at measurement times 1 and 2 if statistical significance is present. In the case of failure of the adaptive measures, non-parametric tests are used as described for ordinal scaled data.

The effect size is given by partial Eta squared and standardised effect size (Cohen's d).

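### The normality check is set on the metric measurements, but the group-by-time test depends on within-patient change, and the mean (SD) change difference in original units is not secured

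*Protocol*

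**What the plan says.** The synopsis (Statistical analysis) and section 5.6.1 give the same sequence for metric endpoints.

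- **What is checked.** "metric data are first tested for normal distribution and significant data outliers using the Shapiro-Wilk test, Q-Q plots and histograms". The synopsis shows what counts as metric when it sets the baseline tests: "for metric data (TUG, TUGman, FSST, 10MWT, eye movements: Saccade velocity, amplitude, latency, fixation duration) the T-test for independent samples". These are the measured variables. Neither change scores nor residuals are named.
- **What follows a failure.** "Non-normally distributed data are transformed using suitable transformation (e.g. ln, square root), checked again and analysed non-parametrically if normal distribution is missing" (5.6.1). The last resort is "In the case of failure of the adaptive measures, non-parametric tests are used as described for ordinal scaled data", which is a Mann-Whitney U test on post-minus-baseline change.
- **The model.** A 2 x 2 ANOVA with time (baseline, post-intervention) within patients and group between patients. The wording "as the basic assumption of a 2 x 2 ANOVA" belongs to homogeneity of variance (Levene), not to normality. A change variable is created only in the ordinal-data route.
- **What the analysis is for.** It is preliminary. It is meant to show trends and to supply the basis for a main-trial sample size with at least 80% power, "using mean (SD) differences between groups".
- **What is reported regardless.** Metric variables are described by mean with 95% CI or SD.

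**The concern.** With only two time points, the group-by-time comparison uses nothing from each patient except the change. Times such as the TUG can be right-skewed between patients while their changes are well behaved. A check on the measurements can then push an endpoint to a log or rank scale for a reason that does not bear on the validity of that comparison.

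Two things are at stake. The first is some power, if the true effect is an absolute one. The second matters more for a pilot: on the log route the inferential estimate is no longer in seconds or m/s, and on the rank route there is no mean difference at all. The endpoints may also finish on different scales.

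**Working it through.** **Sample size used.** Section 4.1.2.3: N = 30/(1 - 10/100) = 33.3, rounded up to 34, or 17 per arm. The plan's figure reproduces.

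**The group-by-time test is a t-test on change.** Let d be post minus baseline, n the number per arm, D the difference between the arm means of d, and s² the pooled variance of d.

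- Interaction sum of squares = nD²/4, on 1 df.
- Error mean square = s²/2, on 2n - 2 df.
- F = (nD²/4)/(s²/2) = nD²/(2s²) = D²/(s² × 2/n) = t².

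In one simulated data set both came to 0.005524. The shape of the levels does not enter.

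**Inputs for the simulations** (2,000 trials per setting)

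- From section 4.4.4.2 (TUG): SEM 1.75 s, so the SD of change from measurement error alone is 1.75 × √2 = 2.47 s. From the MDC of 3.5 s, if it is a 95% MDC, 3.5/1.96 gives about 1.8 s. The two figures come from different cited studies, so both were used.
- Assumed, not in the protocol: log-normal baseline with median 11 or 12 s and log-SD 0.2 to 0.5; normal, additive change; a switch when any of the four arm-by-time cells fails Shapiro-Wilk at 5%.

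**Setting A: 17 per arm, SD of change 1.8 s, order raw, ln, square root, Mann-Whitney; true difference 1.8 s for power**

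| log-SD | Leaves original scale | Power, rule | Power, t-test on change | Loss (points) |
|---|---|---|---|---|
| 0.2 | 29-31% | 0.798 | 0.804 | 0.6 |
| 0.3 | 45-46% | 0.765 | 0.788 | 2.3 |
| 0.4 | 61-65% | 0.754 | 0.800 | 4.6 |
| 0.5 | 75-82% | 0.701 | 0.778 | 7.7 |

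Rejection under the null was 0.042 to 0.048. The verdict at p<0.05 differed from the t-test on change in 2-13% of trials.

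**Setting B: 15 or 17 per arm, SD of change 2.47 s, log-SD 0.3 to 0.5, order raw, ln, Mann-Whitney**

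- The check on measurements left the original scale in 41-72% of trials (23-42% to log, 18-31% to ranks).
- The check on change, per arm, flagged 9-10%. Two 5% tests give 1 - 0.95² = 9.75% by chance.
- The t-test on change rejected in 4.6-5.6% under the null.
- With an assumed 2 s difference (15 per arm, log-SD 0.4), power was 56% for the t-test on change, 51% for Mann-Whitney on change and 41% on the log scale.

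**Setting C: change proportional to baseline, 15 per arm**

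- The changes themselves failed the check in 28% (log-SD 0.4) and 47% (log-SD 0.5) of trials.
- With an assumed 15% effect at log-SD 0.5, power was 80% on the log scale and 58% for the t-test on raw change.

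**Do the descriptive tables supply the planning figure?** They give an SD at each time point. The variance of change is SDb² + SDp² - 2r × SDb × SDp, where b and p are the two time points and r is the within-patient correlation. With equal SDs the SD of change is SD × √(2(1 - r)). At r = 0.80, borrowing the TUG test-retest ICC in 4.4.4.2 purely as an illustration, that is 0.63 × SD. The tables do not report r, so the SD of change cannot be recovered from them.

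**The case against.** Several points against this are fair.

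- **A reader might infer that the mean difference is lost.** The protocol does not support that. Metric means with SD or CI are reported without any condition on the check, and nothing forbids tabulating raw change. What stands is that the SD of change is not secured.
- **A reader might infer that the check on levels is irrelevant.** It is not irrelevant everywhere. The levels enter the baseline t-tests and the group comparisons at times 1 and 2 that follow a significant ANOVA. The rank fallback already works on change.
- **A reader might infer that every move to the log scale is needless.** That holds only if change is roughly additive. Under proportional change the log route gains power (setting C), and the protocol does not settle which applies.
- **The simulated trigger is one reading of the rule.** The protocol gives ln and square root as examples, sets no order, and lists Q-Q plots and histograms beside Shapiro-Wilk. The percentages depend on that reading.
- **Such detail can be left to a SAP.** Often so, but here the protocol states the rule and names the variables. The point concerns what is stated.
- **The analysis is preliminary and mostly secondary.** True. The FGA total is treated as ordinal and never meets this check. The eye-movement measures during FGA items 5, 6 and 10, a listed primary endpoint, do.

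**Conclusion.** The concern holds in a limited form. For the group-by-time comparison, the rule as written checks the measurements when the relevant quantity is within-patient change or the model residuals. This part is exact and needs no assumption.

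The size does rest on assumptions. With skewed levels, normal additive change and a Shapiro-Wilk trigger in any cell, about 30-80% of analyses leave the original scale, against about 10% if change is checked. Power falls by roughly 0 to 8 points, and there is no type I error problem. If change is proportional to baseline, the direction can reverse.

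The practical consequence is that the between-arm difference in mean change and its SD, in original units, is not guaranteed for every metric endpoint, although the same paragraph makes mean (SD) differences the basis for sizing the main trial. The scope is TUG, TUGman, FSST, 10MWT and the eye-movement measures.

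**What to change.** In the synopsis and section 5.6.1:

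1. Apply the normality and outlier check for the group-by-time comparison to within-patient change, or to the model residuals, per arm.
2. For every metric endpoint, report the between-arm difference in mean change with its SD and 95% CI in original units, whatever the check shows.
3. Keep the transformed or rank analysis for endpoints whose change scores or residuals are themselves clearly non-normal.

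This is a change of wording, with no new data or visits. The cost is one extra set of estimates per endpoint. The transformed analysis should not be demoted in every case, because it can be the better one when change is proportional.

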#### **4.1.2.3 Number of participants and sample size**

For this study, 34 people with Idiopathic Parkinson's Syndrome will be included. Of the 34 people with Parkinson's disease, 17 will be randomised to intervention group 1 and 17 to control group 2.

According to Julious, participants per group are considered a minimum sample size for a pilot study. (Julious, 2005) while Browne specifies a number of participants of 30 for a two-arm study. (Browne, 1995). Therefore, to evaluate the feasibility criteria and preclinical effects of the experimental intervention compared to the conventional control intervention, a sample size of 34 is aimed for, based on 30 participants, including an expected failure rate of 10% and using the formula  $N = n / (1 - (z/100))$ . Here, n is the number of participants (30) and z is the expected failure rate (10%).

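### For the metric endpoints the protocol fixes partial eta squared, which is unsigned and biased upwards, and a Cohen's d with no defined contrast, and states no interval for the between-group effect

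*Protocol*

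**What the plan says.** The synopsis (Statistical analysis) ends with: "Effect size is reported using partial Eta squared and standardised effect size". Section 5.6.1 closes in the same way and names the second measure: "The effect size is given by partial Eta squared and standardised effect size (Cohen's d"). In both places the sentence follows the description of the 2 x 2 ANOVA, which has time (baseline, post-intervention) as the within-person factor and group as the between-person factor.

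That ANOVA is for the metric variables, which both places list as TUG, TUGman, FSST, 10MWT and the eye-movement parameters (saccade velocity, amplitude, latency, fixation duration). Eye movements during FGA items 5, 6 and 10 are listed as a primary endpoint in the synopsis and in Table 2 (section 4.3.3). The FGA total is listed as ordinal, and its change scores go to the Mann-Whitney U test.

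The descriptive summary of metric variables in section 5.6.1 is "by mean (95% confidence interval, CI or standard deviation, SD"). The inferential analysis is meant to detect trends in effectiveness and to serve "as a basis for sample size calculation for a randomised controlled trial with sufficient power of at least 80" per cent. That sentence goes on to say that the calculation uses mean differences and SDs between groups.

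**The concern.** An analysis of 30 to 34 patients that looks for trends should tell the reader three things about each endpoint: which arm did better, by how much in usable units, and how uncertain that is. The stated measures do this poorly.

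- Partial eta squared is a proportion of variance. It cannot be negative, so benefit and harm of equal size give the same value. In small samples its expected value is above zero when there is no effect.
- The sentence does not say which term of the ANOVA it applies to. Only group x time carries the treatment comparison. The time term would reflect change common to both arms, all of whom also receive inpatient rehabilitation (section 4.2.2).
- Cohen's d has a sign, but its contrast is not identified: it could be the difference in change or the difference at one time point. The only pairwise comparisons described are between groups at each time point, and only after a significant ANOVA.
- The one 95% interval mentioned for metric variables belongs to descriptive means and is an alternative to the SD. No interval is stated for the between-group effect. Baseline and post-intervention means with SDs do not allow a reader to build one for the difference in change, because the within-person correlation is also needed.

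**Working it through.** **Inputs.** Section 4.1.2.3 plans "17 will be randomised to intervention group 1 and 17 to control group 2", a total "based on 30 participants, including an expected failure rate of 10% and using the formula" N = n/(1 − z/100). The significance level is 0.05 (section 5.6.1). Sidedness is not stated. Two-sided is assumed because the hypotheses in 2.4 and 2.5 are non-directional.

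**The plan's own figure.** 30/(1 − 0.10) = 33.3, rounded up to 34. The stated sample size is reproduced. The calculations below use N = 34 (17 per arm) and N = 30 (15 per arm).

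**Bias of partial eta squared.** With two time points, the group x time test is equivalent to a t-test on change scores, with F = t² on 1 and N − 2 degrees of freedom, and partial eta squared = F/(F + N − 2). With normal errors and no effect, this follows a Beta(1/2, (N − 2)/2) distribution with mean 1/(N − 1):

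- N = 34: 1/33 = 0.030
- N = 30: 1/29 = 0.034

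One million simulated null t values for each N gave 0.0303 and 0.0345. Simulating 10,000 two-time-point data sets with 34 patients gave 0.031. Taking 0.06 purely as an illustrative value, partial eta squared exceeds it under no effect with probability 0.163 (N = 34) or 0.192 (N = 30). In the same simulations omega squared for this term averaged about 0.000.

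**Behaviour of d under no effect** (standardised by the SD of change):

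| | N = 34 | N = 30 |
|---|---|---|
| Mean signed d | 0.00 | 0.00 |
| Mean absolute d | 0.28 | 0.30 |
| Median absolute d | 0.23 | 0.25 |

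**Interval around d = 0.** Half-width = t(0.975, N − 2) × √(2/n per arm):

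- 17 per arm: 2.037 × 0.343 = 0.70
- 15 per arm: 2.048 × 0.365 = 0.75

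So an observed effect of zero would be compatible with a difference of about 0.7 SD of change in either direction. None of the reporting described for the ANOVA shows this.

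**The case against.** The strongest reply is that partial eta squared is not reported alone. Cohen's d is signed and averages zero under no effect, group means are reported, and the protocol plans mean differences with SDs, so direction can be recovered. That stands, and it limits the point to the quality of the reporting.

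A reader might go further and infer that, with no true effect, the pilot would on average report an effect of d = 0.35 to 0.38. Those figures are the mean partial eta squared converted by 2√(η²/(1 − η²)): 0.354 at N = 34 and 0.378 at N = 30. They match the root mean square of d, not its average. The average signed d is zero and the average absolute d is 0.28 to 0.30. Nor does chance give a positive effect size in every endpoint: that is true of partial eta squared only.

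A reader might also infer that the bias would lead to a main trial of 110 to 126 per arm, the size that d = 0.38 or 0.35 would give at 80% power. The synopsis and section 5.6.1 both base that calculation on mean differences and SDs, so the protocol does not plan that route.

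Three further replies are fair. Whether d carries an interval is often left to an analysis plan, which is not at hand, so the missing interval would be weak ground by itself. The Hedges correction at 28 to 32 degrees of freedom is about 0.973 to 0.976, a change of less than 3%. Omega squared does not show which arm did better either. These replies shape the remedy, but they do not defend the choice of measures, which the protocol makes itself in two places.

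**Conclusion.** The point holds in a limited form. The protocol fixes a poor effect measure for the metric endpoints. It is unsigned, its mean for group x time under no effect is 0.030 to 0.034 at 34 to 30 patients, and neither its ANOVA term nor the contrast for d is identified. No interval is stated for the between-group effect, although d is uncertain by about ±0.70 to ±0.75 at this sample size. The timed secondary tests and the eye-movement parameters are affected, including the eye-movement primary endpoint. The FGA total and the sizing of the later trial are not. The figures assume normal errors, equal arms and a d standardised by the SD of change. The point concerns how results are reported; it does not invalidate the ANOVA.

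**What to change.** In the synopsis and in section 5.6.1, replace the effect-size sentence with wording such as: *For each metric endpoint, the between-group difference in change from baseline to post-intervention (group 1 minus group 2) is reported in the endpoint's own units with its 95% CI. A signed Cohen's d or Hedges' g for the same contrast is given with its 95% CI.*

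Set the difference beside the benchmarks in section 4.4 where these exist. Among the metric endpoints that means TUG (MDC 3.5 s, section 4.4.4.2) and 10MWT (MCID 0.18 m/s at comfortable and 0.25 m/s at maximum speed, section 4.4.8.2). Section 4.4 gives no MDC or MCID for TUGman, FSST or the eye-movement parameters.

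Drop partial eta squared. If a variance-explained measure is kept, use omega squared for the group x time term only. The weekly eye-movement recordings during training are made in group 1 only (Table 2), so this between-group sentence cannot apply to them.

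The cost is one sentence in two places, with no new data. The interval comes from the same analysis run. The one downside is that the reported effects will look less precise, which at this sample size is accurate.
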